#### Group M

Thirty patients in group M will receive acupuncture treatment of 3 sessions per week (every Monday, Wednesday and Friday) for 8 weeks. Patients will not be allowed to take any analgesic or anti-inflammatory medications during the trial. In cases of intolerable knee pain, the patients will be instructed to take Tylenol as a rescue medication. The usage of Tylenol will be documented by the outcome assessors. The use of other treatments, such as injections of any kind, moxibustion, ear acupuncture or cupping, will not be allowed.

#### Group L

Thirty patients in group L will receive acupuncture treatment once per week (every Monday, Wednesday or Friday) for 8 weeks. Other interventions will be similar with group M.

### Outcomes

If only one knee is affected, the assessment of the outcomes will relate to this knee. If the patient has two affected knees of which only one meets the ACR criterion and Kellgren–Lawrence grade II or III, only this knee will be evaluated. In the case that both knees are affected in accordance with the inclusion criteria (ACR and Kellgren–Lawrence grade II or III), the more painful knee will be randomly chosen for evaluation.

#### Primary outcome measurement

The response rate is the percentage of patients with improvement in average pain (NRS) of at least 2 units and in the Western Ontario and McMaster Universities Osteoarthritis Index [31] (WOMAC) function subscale score of at least 6 units at week 8 compared with baseline. The pain NRS is a self-administered instrument, a number selected from 0 to 10 by the patient. The intensity of pain range (over the past week) is from 0 = no pain to 10 = worst possible pain. The WOMAC function subscale refers to the participant’s ability to move around and perform usual activities of daily living. It is comprised of 17 questions (each question ranged from 0 to 4) regarding the degree of difficulty experienced due to osteoarthritis in the study of the knee, with higher scores indicating worse physical function.

#### Secondary outcome measurements

Knee pain will be assessed by the NRS and the WOMAC pain subscale (five items, scored from 0 to 20, higher scores indicating worse pain) at weeks 4, 8 and 16. The WOMAC function subscale will be used to measure physical function at weeks 4, 8 and 16. The WOMAC stiffness subscale will be used to measure the degree of stiffness experienced in the knee at weeks 4, 8 and 16. The Overall Treatment Effect will be used to measure the overall acupuncture treatment effect at weeks 4 and 8. The 12-item Short Form Health Survey [32] (SF-12; scored from 0 to 100, higher scores representing better quality of life) will be used to measure the quality of life at weeks 4, 8 and 16. The Expectation and Credibility of treatment rating scale [33] will be used to measure the patients’ attitudes to acupuncture after the first treatment. The number of adverse events and severe adverse events and the usage of Tylenol will be recorded from baseline to week 16.

#### Data collection, management and monitoring

To promote patient retention and complete follow-up, all interventions are free to patients.

The Case Report Form (CRF) will be completed on paper copies and then entered into the Excel spreadsheet by an independent investigator to act as the first level of control to ensure the accuracy of the data. The second level of data integrity will include data monitoring and validation that will be conducted on a regular basis throughout the study. The original CRFs and all other forms (including the consent forms) will be archived securely at the School of Acupuncture-Moxibustion and Tuina, Beijing University of Chinese Medicine. The Research Ethical Committee of Beijing Hospital of Traditional Chinese Medicine Affiliated to Capital Medical University will audit the trial conduct every 5 months independently of investigators and the sponsor, and will decide on any premature closure of the study.

### Sample size

The current study is designed as a pilot study to explore symptomatic improvement in patients with knee osteoarthritis receiving 3 sessions per week of acupuncture compared to 1 session per week. Acupuncture as a complex intervention is different from drugs. If the acupoints in the study were changed, then the effectiveness of the acupuncture would be altered. Consequently, we do not use data from the literature to calculate the sample size. We based our sample size on the response rate. Based on our previous study (unpublished) and clinical experience, the sample size is calculated to provide 80% power if 70% of group M achieved a decrease ≥ 2 points on the NRS and a decrease ≥ 6 points in WOMAC function score at 8 weeks, compared with 30% of group L, at a two-tailed α level of 0.05. This requires a total of 60 participants, allowing for 20% dropout.

### Statistical analysis

Analyses will be intention-to-treat (ITT), with all patients included in their assigned treatment group and receiving at least one session treatment. The level of significance will be set at 0.05 (two-sided). Patients’ baseline characteristics will be summarized by treatment arm. For continuous outcomes, the data will be presented as mean (standard deviation) or the median (interquartile range) according to the normality of the distribution. Enumeration data will be presented as a percentage. For the primary outcome, we will calculate the response rates at 8 weeks and compare group M and group L using the χ^2^ test. For secondary outcomes, continuous variables including WOMAC pain, function and stiffness scores, NRS, SF-12, the Expectation and Credibility of acupuncture treatment and Overall Treatment Effect will be compared between the two groups at all follow-up time points using an unpaired Student’s *t* test or Wilcoxon rank-sum test as appropriate. For the dropout analysis, we will use the last observation carried forward method. SPSS version 21.0 (IBM SPSS Statistics, New York, USA) will be used for statistical analysis.

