### Randomization and blinding

Patients will be randomly assigned (on a 1:1 ratio) to the more frequent acupuncture treatment group (group M) or the less frequent acupuncture treatment group (group L). The randomization sequence will be computer generated by independent research staff with SAS 9.3 software, using block randomization with a block size of six via a central randomization system. The randomization sequence will be embedded into the software (Beijing Guide Technology Co, Ltd). The CRC will input the patient information on a tablet computer and will be given a random number. The randomization protocol will be designed by a statistician ([name]) of Fuwai Hospital, China Academy of Medical Science who is not involved in the later statistical work of the study.

The outcome assessor and data analyst will be blinded to group assignments. The acupuncturist and patients will not be blinded because of the nature of the intervention. Patients’ allocated interventions will not be revealed until the statistical analysis is completed.

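### The analysis labelled intention-to-treat leaves out randomised patients who receive no session; in an open-label comparison of 24 with 8 visits this may bias the primary result in either direction

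*Protocol article*

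**What the plan says.** The Statistical analysis section defines the analysis population in one sentence: "Analyses will be intention-to-treat (ITT), with all patients included in their assigned treatment group and receiving at least one session treatment". The first part is the intention-to-treat principle. The final clause adds a condition that can only be met after randomisation. The article describes no other analysis of all randomised patients. The same section compares week-8 response rates with a chi-squared test and handles dropout by carrying the last observation forward.

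On blinding, the Randomization and blinding section says "The acupuncturist and patients will not be blinded because of the nature of the intervention", and limits masking to two roles: "The outcome assessor and data analyst will be blinded to group assignments".

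On visit load, the Group M section says "Thirty patients in group M will receive acupuncture treatment of 3 sessions per week (every Monday, Wednesday and Friday) for 8 weeks", which is 3 × 8 = 24 visits. The Group L section says "Thirty patients in group L will receive acupuncture treatment once per week (every Monday, Wednesday or Friday) for 8 weeks", which is 8 visits.

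**The concern.** A rule requiring at least one treatment is usually defended on the ground that, under blinding, failure to start cannot depend on the allocated arm. That defence is not available here. Patients are unblinded and the schedule itself identifies the arm. A patient allocated to three visits a week may decline because of the burden, and a patient allocated to one may decline out of disappointment. Either patient then drops out of the denominator of the primary outcome. If never-starters would have responded differently from those who start, and their numbers differ between arms, the comparison is no longer between the groups as randomised, although it carries the intention-to-treat label.

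The Discussion section recognises that lack of blinding can affect reporting and measurement, and offers an expectation and credibility scale. That scale is completed after the first treatment (Secondary outcome measurements), so it gives no information on patients who never had one.

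**Working it through.** **1. The plan's own sample size.** The Sample size section assumes "80% power if 70% of group M achieved a decrease ≥ 2 points on the NRS" (together with the function threshold), against 30% in group L, with two-sided alpha 0.05 and 20% dropout. The pooled-variance formula without continuity correction gives

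n = [1.96·√(2·0.5·0.5) + 0.8416·√(0.7·0.3 + 0.3·0.7)]² / 0.4² = (1.386 + 0.545)² / 0.16 ≈ 23.3, so 24 per arm.

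Then 24/0.8 = 30 per arm, 60 in total. The stated figure reproduces. The concern is the analysis set and not the sample size.

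**2. Bias from excluding never-starters.** The article gives neither a never-starter rate q nor their response rate r, so both are assumed. With true response p among all randomised patients in an arm, the rate among starters is (p − q·r)/(1 − q). Take p = 0.50 in both arms and r = 0.20.

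- q = 10% in M, 0% in L: (0.50 − 0.02)/0.90 = 53.3% against 50.0%, a spurious +3.3 points for M.
- q = 20% in M, 5% in L: (0.50 − 0.04)/0.80 = 57.5% against (0.50 − 0.01)/0.95 = 51.6%, a spurious +5.9 points for M.
- With the losses reversed, the same amounts favour L.
- With equal q in both arms, or with r = p, the expected bias is zero.

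The 20% case uses the whole dropout allowance (0.20 × 30 = 6 patients) in one arm and is an upper illustration.

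**3. Effect on the test.** Let k patients in M only never start, and suppose that all would be non-responders if counted (r = 0). True rates among all randomised are equal. The rejection probability of the uncorrected chi-squared test at 0.05, by exact enumeration with 30 randomised per arm, is:

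| k excluded from M | M rate at true 50% | Type I error at 50% | Type I error at 30% |
|---|---|---|---|
| 0 | 50.0% | 0.052 | 0.049 |
| 1 | 15/29 = 51.7% | 0.054 | 0.054 |
| 2 | 15/28 = 53.6% | 0.058 | 0.053 |
| 3 | 15/27 = 55.6% | 0.079 | 0.066 |
| 6 | 15/24 = 62.5% | 0.150 | 0.102 |

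One or two never-starters change little; the effect becomes material from about three, all in one arm. A single borderline result can still cross the threshold: 18/30 against 11/30 gives p = 0.071, and 18/28 against 11/30 gives p = 0.036. That example was chosen to be borderline.

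**4. What the plan's missing-data rule would do.** If a never-starter is kept and has no week-8 value, carrying baseline forward gives zero change and hence non-response. The counted rate is p − q·r. Under the assumptions of step 2:

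- 10% against 0%: 48.0% against 50.0%, or −2.0 points for M.
- 20% against 5%: 46.0% against 49.0%, or −3.0 points for M.

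These errors are smaller than those from exclusion and run the other way, but this depends on r. If r = 0.50, exclusion has no expected bias, while this rule gives 45% against 50% in the first case. Only observed week-8 outcomes remove the dependence.

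**The case against.** The other side has several good points.

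- **Timing of disclosure.** The article does not say when patients learn their arm. That they know it before the first session is a reasonable inference, since visits must be booked, but it remains an inference. The closing statement of Randomization and blinding, "Patients’ allocated interventions will not be revealed until the statistical analysis is completed", does not settle the matter the other way: it cannot apply to patients attending on their allocated schedule.
- **Features that reduce non-starting.** Time commitment is discussed before consent (Study setting, recruitment and ethics). Treatment is free, expressly to help retention (Data collection, management and monitoring). Both arms receive real acupuncture. These make differential non-starting less likely without excluding it.
- **Size.** Every magnitude rests on assumed rates. The illustrated 3 to 6 points are small beside the planned difference of 70% − 30% = 40 points.
- **Purpose.** The trial is a pilot and the condition is declared in advance. This tempers the severity. It does not remove the point, because the primary outcome is formally powered and tested, and the result is to inform a decision on a full-scale trial.

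A reader might infer that exclusion is certain to be informative, that the randomised comparison is broken, or that the rule favours group M. The document supports none of these. It shows that not starting could depend on the arm, and the direction depends on which arm loses more patients.

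**Conclusion.** The point holds with moderate severity. That the label and the definition disagree is certain on the text: the set described is modified intention-to-treat. This is a stated definition and not a detail left to an analysis plan. That the exclusion may bias the primary comparison follows from open-label delivery and the 24-against-8 visit contrast. How much, and in which direction, cannot be known from the document. About 3 to 6 points is conditional on never-starter rates of 10% against 0% or 20% against 5%, 50% true response in both arms and 20% among never-starters. If few patients fail to start, or both arms lose similar numbers with similar prognosis, the practical effect will be slight.

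**What to change.** Define the primary analysis set as all randomised patients in their assigned arm, whether or not any session was received. Seek week-8 pain and function scores from never-starters. Where these cannot be obtained, apply the plan's existing last-observation rule from baseline, and state openly that it counts such patients as non-responders and is an assumption. Keep the at-least-one-session set as a sensitivity analysis labelled modified intention-to-treat, and report the number of never-starters by arm. Settle this before the primary comparison is run.

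The cost is one revised sentence and a little follow-up contact. The sample size stays at 60. The estimated difference may be somewhat smaller, particularly if group M loses more patients before the first session.

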**Discussion:**

Three sessions per week of acupuncture treatment may be superior to 1 session per week of acupuncture treatment for symptomatic outcomes in knee osteoarthritis. Results of the study will be of great importance for the guidelines of clinical therapy.

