## Discussion

This study is designed to explore an effective acupuncture method for knee osteoarthritis.

We chose a frequency of 3 sessions per week as one kind of electro-acupuncture intervention, because 3 sessions per week is most commonly used in clinical practice in China to treat chronic pain. We chose a frequency of once per week as another intervention, because electro-acupuncture treatment once per week was usually used in previous studies. The study is a single-site randomized clinical trial. A single-site trial might be helpful in the aspect that the quality of the study procedure will be better controlled in a single site than in multiple sites. One potential limitation of this study is that the unblinded treatment might theoretically influence reporting or measurement of the outcomes, thus introducing bias. Therefore, we will use an Expectation and Credibility of treatment rating scale to measure the patients’ attitudes to acupuncture.

The information obtained from the exploratory study will inform the decision to conduct a full-scale randomized controlled trial to test the frequency dependence of acupuncture, which will add to the current small body of high-quality evidence that is available on the optimal number of sessions of acupuncture for the management of knee osteoarthritis.

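### The stated primary comparison is an unadjusted χ² test; a baseline-adjusted risk difference with its 95% CI would tell the full-trial decision more, at almost no cost

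*Protocol article*

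**What the plan says.** Statistical analysis: "For the primary outcome, we will calculate the response rates at 8 weeks and compare group M and group L using the" χ² test. The same section sets a two-sided 0.05 level, names no covariate for this comparison, and carries the last observation forward for dropouts.

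Primary outcome measurement: a responder must improve by at least 2 points on the pain NRS and by at least 6 points on WOMAC function between baseline and week 8.

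Sample size: "the sample size is calculated to provide 80% power if 70% of group M achieved" both thresholds, "compared with 30% of group L", "at a two-tailed α level of 0.05". The total is 60, with 20% dropout allowed for. The rates come from an unpublished study and clinical experience. No smallest worthwhile difference is given.

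Discussion, on the use of the result: "The information obtained from the exploratory study will inform the decision to conduct a full-scale randomized controlled trial".

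**The concern.** The endpoint is built from two change scores, so where a patient starts affects whether that patient can respond:

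- WOMAC function has 17 items scored 0 to 4, so it runs from 0 to 68. The inclusion criteria set no minimum function score. A patient who enters below 6 cannot meet the function part at all.
- Entry requires an NRS of at least 4. A 2-point drop is half of the available range for a patient at 4 and a fifth of it for a patient at 10.

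In 60 patients, chance imbalance in these scores moves the response rates, and the stated test does not use them.

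The study calls itself a pilot and exploratory, and its stated use is to help decide on a larger trial. For that use, the size of the difference and its uncertainty matter more than whether p falls below 0.05. The test has good power only near the 40-point design gap. At a clearly smaller gap, a non-significant result is likely and does not separate no effect from an effect large enough to study further.

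**Working it through.** **Inputs.** From Sample size: 70% and 30%, power 80%, two-sided α 0.05, 20% dropout, N = 60. From Randomization and blinding: 1:1 allocation, hence 30 per arm. Up to 30 per arm are analysed if last observation carried forward fills all gaps; 24 per arm is 30 × 0.8. The 20-point difference is an assumption.

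**1. The article's own figure.** Pooled-variance formula, no continuity correction:
n = [1.96·√(2·p̄·q̄) + 0.8416·√(p1q1 + p2q2)]² / d².
With p̄ = 0.5, d = 0.4 and p1q1 + p2q2 = 0.42: (1.3859 + 0.5454)² / 0.16 = 23.3, so 24 per arm. Then 24 / 0.8 = 30 per arm, or 60 in total. This matches. Power at 70% versus 30% is 81% with 24 per arm and 89% with 30.

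**2. Power at an assumed 50% versus 30%.** Power ≈ Φ[(d√n − 1.96·√(2·p̄·q̄)) / √(p1q1 + p2q2)], with p̄ = 0.4, so √0.48 = 0.6928 and √0.46 = 0.6782.
- n = 30: Φ[(1.0954 − 1.3579) / 0.6782] = Φ(−0.387) = 34.9%. Exact enumeration of the Pearson test gives 35.1%.
- n = 24: Φ[(0.9798 − 1.3579) / 0.6782] = Φ(−0.557) = 28.9%. Exact: 31.0%.

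The exact chance of non-significance is therefore 65% (30 per arm) or 69% (24 per arm).

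**3. Dependence on the base rate.** Chance of a non-significant result at a 20-point gap, normal approximation (exact Pearson in brackets):

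| Group L → M | 30 per arm | 24 per arm |
|---|---|---|
| 10 → 30% or 70 → 90% | 51% (50%) | 59% (57%) |
| 20 → 40% or 60 → 80% | 61% (61%) | 68% (67%) |
| 30 → 50% or 50 → 70% | 65% (65%) | 71% (69%) |
| 40 → 60% | 66% (65%) | 72% (69%) |

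**4. What an interval adds.** Suppose 15/30 versus 9/30 respond.
- Test: pooled rate 0.4, SE = √(0.24 × 2/30) = 0.1265, z = 0.20 / 0.1265 = 1.58, p about 0.11.
- Interval: 0.20 ± 1.96·√(0.46/30) = 0.20 ± 0.243, or −4 to +44 points.

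The test reads as not significant. The interval includes zero and also the full 40-point design effect. With 9/30 in group L, significance needs 17/30 in group M (a 27-point observed gap, z = 2.08); 16/30 gives z = 1.83.

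**5. What baseline adjustment adds.** Simulations under assumed score distributions, with baseline to week-8 correlations of 0.3 to 0.7, put the variance of the adjusted risk difference between about 0.87 and 1.0 times the unadjusted variance. At the favourable end:
- Half-width at 50% versus 30%, 30 per arm: 24.3 × √0.87 = 22.6 points.
- Effective sample: 30 / 0.87 = 34.5 per arm, so power = Φ[(0.2·√34.5 − 1.3579) / 0.6782] = about 39%, against 35%.

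At the unfavourable end nothing changes.

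**The case against.** Nothing in the Sample size or Statistical analysis sections is miscalculated. An unadjusted χ² test is valid under 1:1 randomisation, and any trial has low power at half its design effect. The article states its target effect and the source of that effect openly. Intervals and covariate models are often left to a full protocol or analysis plan, and the article says that a full protocol exists. The adjustment gain is small, and zero in the less favourable scenarios. All of this stands, and it limits the point to a better choice of primary comparison.

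Three stronger readings are tempting, and the document supports none of them.
- A reader might infer that a p-value is the only primary output. The same sentence also plans the response rate in each arm, from which a difference can be worked out.
- A reader might infer that the full-trial decision turns on p < 0.05. No such rule is stated. The Discussion refers to the study's information in general, which also covers the secondary outcomes and adverse events.
- A reader might treat 20 points as an agreed worthwhile effect. No section gives such a threshold.

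The abstract's line "Results of the study will be of great importance for the guidelines of clinical therapy" is promotional wording, not an analysis choice, and this point does not depend on it.

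What the objection does not remove is that the article itself fixes the comparison as an unadjusted test. That is a stated choice, not an omission, and a better one is available from data already collected.

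**Conclusion.** The point holds as a modest improvement to a stated method, not as an error. The sample size is right. The stated between-group primary comparison ignores the two baseline scores that define the endpoint. If the true gap were 20 points, the test alone would be non-significant in about 51% to 66% of trials with 30 per arm for group L rates from 10% to 70%, and in about 65% (30 per arm) to 69% (24 per arm) at 50% versus 30%.

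Two assumptions carry these figures: the 20-point gap, and an uncorrected Pearson test. With a Yates or Fisher test at 50% versus 30%, non-significance rises to 74% (30 per arm) or 79% (24 per arm).

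Most of the benefit comes from leading with an estimate and its interval. Adjustment adds roughly 0% to 13% lower variance, depending on score distributions that the article does not give. It does not turn 60 patients into an adequate sample for a 20-point effect: on the formula in step 1, 80% power at 50% versus 30% needs 93 per arm before dropout.

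**What to change.** In Statistical analysis, state that the primary result is the difference in week-8 response rates (group M minus group L) with its 95% CI, adjusted for baseline NRS and baseline WOMAC function. Name one model in advance: either a logistic model standardised to give a risk difference, or a linear model with robust standard errors, in which the group coefficient is the risk difference directly. Keep the unadjusted rates per arm and the χ² test as supporting results.

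The cost is one extra model and a few lines of text. No patient, visit or measurement is added, and the sample size calculation can stay as it is.

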### Inclusion criteria

Age 45–75 years, male or female.Diagnosis of knee osteoarthritis according to the American College of Rheumatology (ACR) criteria [28].Symptoms have been present for more than 6 months.Radiologic confirmation of knee osteoarthritis (Kellgren–Lawrence grade [29] II or III in the recent 6 months).An average knee pain severity over the past week of ≥ 4 out of 10 on an 11-point numerical rating scale (NRS) [30].Agreed to refrain from the use of any analgesics during the trial (paracetamol sustained-release tablets will be given to patients if their pain intensity reaches ≥ 8 out of 10 on an 11-point NRS).Signed informed consent.

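### The continuous secondary scores are tested visit by visit without a baseline term, which gives up precision that the recorded baselines could supply

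*Protocol article*

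**What the plan says.** The Statistical analysis section of the protocol article lists "continuous variables including WOMAC pain, function and stiffness scores, NRS, SF-12, the Expectation and Credibility of acupuncture treatment and Overall Treatment Effect" and states that these "will be compared between the two groups at all follow-up time points", using an unpaired t test or a Wilcoxon rank-sum test as appropriate. It names no covariate, change score or model for repeated measures. Baseline enters that section only descriptively: "baseline characteristics will be summarized by treatment arm".

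Under Secondary outcome measurements, NRS, the three WOMAC subscales and SF-12 are each scheduled three times; for example, "The WOMAC function subscale will be used to measure physical function at weeks 4, 8 and 16". Overall Treatment Effect is scheduled at weeks 4 and 8, and the expectation and credibility scale once, after the first treatment.

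Under Primary outcome measurement, response needs an NRS improvement of at least 2 units and an improvement in the WOMAC "function subscale score of at least 6 units at week 8 compared with baseline". Baseline values of these two scores must therefore exist.

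**The concern.** In a trial with 30 patients per arm, a patient's starting score is usually the most useful predictor of the later score. Testing follow-up scores alone leaves the variation explained by baseline in the error term. The intervals on pain and function are then wider than they need be.

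This matters because the Discussion says that the results will inform a decision on a full-scale trial, and the size and precision of the differences in pain and function bear on that decision. The sample size was set for the binary response only. The continuous scores have no sizing of their own, so their precision depends on how well the analysis uses the data.

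**Working it through.** **The plan's own figure.** Inputs from the Sample size section: 70% versus 30% response, 80% power, two-sided 0.05, 20% dropout. With pooled variance under the null and no continuity correction:

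n per arm = [1.96·√(2·0.5·0.5) + 0.842·√(0.7·0.3 + 0.3·0.7)]² / 0.4² = (1.386 + 0.545)² / 0.16 = 23.3, rounded up to 24.

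Dropout: 24 / 0.8 = 30 per arm, 60 in total. The stated figure reproduces. It rests on the response rate alone, so nothing below changes it.

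**Inputs for the secondary scores.** 30 per arm as randomised, or 24 per arm after the planned dropout. The documents give neither r nor a standard deviation. I assume r = 0.3, 0.5 and 0.7, equal SDs at baseline and follow-up, and express differences in SD units. The 0.5 SD difference is only an illustration.

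**Formulas.** Variance of the between-group difference, relative to an unadjusted comparison of follow-up scores:
- ANCOVA: 1 − r²
- change score: 2(1 − r)
- interval width under ANCOVA: √(1 − r²)
- equivalent unadjusted trial size: N / (1 − r²)

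Power uses the noncentral t distribution with noncentrality d·√(n/2) / √(1 − r²), on 2n − 2 degrees of freedom unadjusted (r set to 0) and 2n − 3 for ANCOVA.

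| | Unadjusted | r = 0.3 | r = 0.5 | r = 0.7 |
|---|---|---|---|---|
| ANCOVA variance ratio | 1 | 0.91 | 0.75 | 0.51 |
| Variance reduction | – | 9% | 25% | 49% |
| Interval narrower by | – | 4.6% | 13.4% | 28.6% |
| Change-score variance ratio | – | 1.4 | 1.0 | 0.6 |
| Detectable at 80% power, 30 per arm (SD) | 0.74 | 0.70 | 0.64 | 0.53 |
| Power for 0.5 SD, 30 per arm | 48% | 51% | 59% | 76% |
| Equivalent unadjusted total, from 60 | 60 | 66 | 80 | 118 |
| Detectable at 80% power, 24 per arm (SD) | 0.83 | 0.79 | 0.72 | 0.59 |
| Equivalent unadjusted total, from 48 | 48 | 53 | 64 | 94 |

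**Downside.** At r = 0, with 30 per arm, the detectable difference is 0.7358 SD adjusted and 0.7356 SD unadjusted. Adjustment costs almost nothing even if baseline predicts nothing.

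**Change scores.** 2(1 − r) − (1 − r²) = (1 − r)², which is positive for any r below 1. ANCOVA is therefore more precise than change scores as well.

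**Chance imbalance.** With 30 per arm, the standard error of a baseline mean difference is √(2/30) = 0.258 SD. A gap of that size shifts the unadjusted follow-up difference by r × 0.258, which is 0.08, 0.13 or 0.18 SD for the three values of r. Adjustment removes this component; the unadjusted standard error already allows for it.

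**The case against.** The strongest reply is that these are secondary outcomes in a trial labelled pilot and exploratory. The primary outcome uses baseline through its definition, and no confirmatory claim rests on the t tests. That stands, and it limits the weight of the point.

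The gain is also uncertain. It is small at r = 0.3, and the entry rule "An average knee pain severity over the past week of ≥ 4 out of 10" restricts the baseline range and may lower r for NRS. That stands too. The variance figures apply to comparisons of means, so they do not carry over exactly where the rank-sum test would be used.

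The text does not say outright whether follow-up scores or changes are tested. Follow-up scores are the natural reading. A change-score analysis would use baseline, though less efficiently than ANCOVA.

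It could be said that covariates belong in an analysis plan that is not shown. But the article positively names the tests, so this is a stated choice and not an omitted detail.

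A reader might infer more than the documents support:
- **Invalid or biased comparisons.** Randomisation keeps the unadjusted difference unbiased on average with respect to baseline.
- **A large overall false-positive rate from counting every outcome and visit.** Such a figure needs independent tests, and these are related scales measured repeatedly in the same patients.
- **Per-visit tests force imputation.** They can be run on the patients observed at each visit; last observation carried forward is a separate choice in the plan.
- **The test is chosen by a normality check.** The article ties normality to how data are presented; for the tests it says only that the choice will be made as appropriate.

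**Conclusion.** The point holds as a loss of precision on NRS, the WOMAC subscales and SF-12. Under assumed r from 0.3 to 0.7, baseline adjustment removes 9% to 49% of the variance and narrows intervals by about 5% to 29%. These figures rest on assumed correlations and equal SDs, neither of which the documents give.

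The remedy is certain to be available only for NRS and WOMAC function. The text does not state baseline collection of WOMAC pain, stiffness and SF-12, and the schedule figure is not shown, so its absence from the text is no evidence that they are not collected. Expectation and credibility and Overall Treatment Effect are outside the point because they have no baseline value to adjust for.

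**What to change.** For each repeated score with a baseline value, replace the separate two-group tests with either ANCOVA at each visit or one mixed model for repeated measures over weeks 4, 8 and 16. The mixed model should contain arm, visit, arm-by-visit and the baseline score. Apply this to NRS and WOMAC function, and to WOMAC pain, stiffness and SF-12 if the schedule records their baselines.

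Report adjusted mean differences with 95% confidence intervals. Name week 8 as the main time point, to match the primary outcome. This needs its own sentence, because a model with arm-by-visit still yields an estimate at each of the three visits.

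Keep the simple tests for Overall Treatment Effect and for expectation and credibility.

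The cost is a change to the analysis wording. It adds no visits or patients, and no new measurements for NRS and WOMAC function. The article reports that recruitment is under way, so the change can still be specified before the analysis.
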